### Outcomes

#### Primary outcomes

Rate and duration of hospital re-admissions of patients with unipolar disorder and bipolar disorder, respectively, as according to data retrieved from the Danish Psychiatric Central Register [40]

#### Secondary outcomes

Severity of depressive symptoms and manic symptoms (manic symptoms only for patients with a bipolar disorder diagnosis) measured using the HDRS-17 and the YMRS, respectivelyPsychosocial functioning according to the Functional Assessment Short Test (FAST)Number of depressive episodes and manic episodes (manic episodes only for patients with a bipolar disorder diagnosis) defined as HDRS-17 > 13 and YMRS >13, respectivelyAutomatically generated behavioral data measured as an aggregated composite measure

#### Tertiary outcomes

Perceived stress according to Cohen’s Perceived Stress Scale [54], quality of life according to the WHO Quality of Life-BREF (WHOQOL-BREF) [55], self-rated depressive symptoms according to Beck’s Depressive Inventory (BDI) [56–60], self-rated depressive symptoms according to the Hamilton Depression Self-rating Scale 6-item (HDRS-6) [59], self-rated manic symptoms according to the Altman Self-rating scale for Mania (ASRM) (only for patients with a bipolar disorder diagnosis) [34], recovery according to the Recovery Assessment Scale [60], empowerment according to Roger’s Empowerment Scale [61], adherence to medication according to the Medicine Adherence Rating Scale [62], wellbeing according to the WHO (five) Wellbeing Index [63], rumination according to the Ruminative Response Scale (RRS), worrying according to the Penn State Worry Questionnaire (PSWQ) [64], and satisfaction according to the Verona Satisfaction Scale-Affective Disorder (VSS-A) [65]

No changes in trial outcomes have been made after trial commencement.

### Statistical power and sample size calculation

The statistical power and sample size was calculated using http://stat.ubc.ca/~rollin/stats/ssize/n2.html.

The primary outcomes are differences in the number and duration of re-admissions to a psychiatric hospital between the intervention group and the control group − analyzed separately according to psychiatric diagnosis (unipolar disorder or bipolar disorder). Power calculations are similar for the two RCTs/patient groups (unipolar disorder or bipolar disorder). Based on prior findings aiming to reduce re-hospitalization due to recurrent depression [66] and bipolar disorder [9], combined with presumptions of positive effects of the immediate early contact with patients during the vulnerable period following discharge from a psychiatric hospital, regardless of diagnosis, we expect a reduction in re-admissions from 30% to 15% in the intervention group using smartphone-based treatment. Thus, anticipating a hazard ratio (HR) of 0.50 in the comparison of the intervention group with the control group on the primary outcome, a two-sided risk of type 1 error, *α* of 0.05, a type 2 error risk, *β*, a statistical power of 80%, the sample size (*N*) is calculated as *N* = 200 (100 patients in each arm of each RCT) per RCT and, thus, a total of 400 patients (200 patients with unipolar disorder and 200 patients with bipolar disorder) is estimated to be required for the RADMIS trial. Cumulated durations of re-hospitalizations comprise similar power calculations and sample sizes. Regarding the secondary outcomes, the clinically relevant difference in depressive or manic symptoms is defined as a minimum of three scores on the HDRS-17 or on the YMRS, respectively, and the standard deviation (SD) is set at 7 with a mean score of 12 versus 15 in the intervention group and the control group, respectively. The statistical power to detect a three-score difference in the areas under the curves between the intervention and the control groups on the HDRS-17 or the YMRS, respectively, is 80% with *α* = 0.05 for a two-sample comparison of means including a total of 200 patients (100 patients in each arm) in each of the two RADMIS RCTs.

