### Randomization

#### Sequence generation

A computer-generated list of random allocation numbers using Pharma Consulting Group (http://www.pharmaconsultinggroup.com) will be generated. Patients included in the trial are randomized with a balanced allocation ratio of 1:1 to (1) using the Monsenso system, including the integrated feedback loop, based on a combination of subjective self-monitored measures and automatically generated behavioral data on measures of illness activity) including context-aware CBT modules (the intervention group) or to (2) standard treatment-as-usual (the control group) (Fig. 1).

Since the RADMIS trial is single-blinded, random block sizes are used to help preserve unpredictability [67, 68]. The RADMIS study nurses are unaware of the range of numbers in the block sizes.

The study will use a stratified design, where patients are stratified according to the psychiatric centres where patients are discharged from and according to the number of previous hospitalizations (three or less or more than three). The statistical analyses will adjusted for the two stratification variables, and also age and sex as possible prognostic variables. Further, in analyses on continuous variables, potential differences in baseline score on the outcome in question will be included as a potential confounder. If there are no statistically significant main effects of age and sex, these variables will be excluded from the final statistical analyses.

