### Statistical methods

Data from all randomized patients are collected until dropout or the end of the trial period. Analysis will be carried out with an intention-to-treat (ITT) approach. The primary outcomes are differences in time to re-admission and duration of re-admissions during the 6-month trial period between the intervention group and the control group. Time to the first re-admission will be estimated using a Kaplan-Meier plot with reasons for censoring being date of death or end of study. The differences in cumulated prevention of re-admission in the intervention group and the control group will tested using a log-rank test. Analysis of secondary and tertiary outcomes will be done employing a linear mixed-effects model with random intercept for each participant and a fixed effect of visit. Differences in outcomes between the intervention group and the control group will be analyzed, firstly in an unadjusted model (except for differences in baseline values of the outcome variable in analyses on continuous variables) and then in models adjusted for the two stratification variables (1) psychiatric center and (2) the number of prior hospitalizations, and also for age and sex as possible prognostic variables. If there are no statistically significant main effects of age and sex, these variables will be excluded from the final analyses. Furthermore, subanalyses will be done employing a linear mixed-effects model with random intercept for each participant and a fixed effect of visit on differences in the HDRS-17 and the YMRS in patients with the presence of depressive and manic symptoms (defined as HDRS-17 > 0 or YMRS >0, respectively) at a given time point during the trial period between the intervention group and the control group. Additionally, in addition to analyses of the secondary outcomes, we will analyze differences in depressive and manic episodes defined as HDRS ≥14 and YMRS ≥14, respectively, during the trial period. Potential interactions between randomization group and visit number on any specific outcome variable in the analyses will be investigated and reported accordingly. The statistical threshold for significance is *p* ≤ 0.05 (two-tailed). Data will be managed by [name] and entered using Epidata®. All analyses will be done using SPSS, version 22.0 (IBM, New York, NY, USA) and STATA version 12 (StataCorp LP, College Station, TX, USA).

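### With 200 patients per trial, the plan's own inputs give about 71–75% power (30% vs 15%) or 62–66% (HR 0.50) for re-admission, not the stated 80%; the two effects also differ.

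*Protocol article*

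**What the plan says.** The section on statistical power and sample size calculation in the protocol article sets out the design effect in two steps. First, "we expect a reduction in re-admissions from 30% to 15% in the intervention group using smartphone-based treatment". From this it infers the second, "anticipating a hazard ratio (HR) of 0.50 in the comparison of the intervention group with the control group on the primary outcome". The error rates are "a two-sided risk of type 1 error, *α* of 0.05" and "a statistical power of 80"%, and the result is N = 200, that is "100 patients in each arm of each RCT) per RCT", for each of the two trials. The same section says that the calculation for cumulated duration of re-hospitalisation is similar.

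The Statistical methods section names the test for time to first re-admission: "The differences in cumulated prevention of re-admission in the intervention group and the control group will tested using a log-rank test". It describes the primary outcomes as "differences in time to re-admission and duration of re-admissions during the 6-month trial period". Allocation is balanced. The Advantages part of the Discussion says that register data on re-admission will be available for every included patient, whether or not they drop out.

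**The concern.** Every input to the calculation is printed, so the figure can be checked without the full protocol or an analysis plan. Two things look wrong. The sample size is smaller than standard formulas give for these inputs. A halving of risk is also carried over as a hazard ratio of 0.50, although the two differ when the event proportion is as high as 30%.

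This is the only power statement for the primary question, it serves two separate trials, and the duration outcome leans on it. If the true power is well below 80%, a non-significant result in either trial would be read as stronger evidence against the intervention than the design supports.

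**Working it through.** **Inputs** (sample-size and Statistical methods sections): re-admitted 30% in control and 15% in intervention; HR 0.50; two-sided alpha 0.05 (z = 1.960); power 80% (z = 0.842); 100 per arm, 1:1; log-rank test over 6 months; no loss to follow-up for the register outcome. One assumption is needed: the 30% is the proportion of patients with a first re-admission within 6 months.

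**1. Trying to reproduce 100 per arm from 30% vs 15%**

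- Pooled variance, mean proportion 0.225: n = [1.960·√(2·0.225·0.775) + 0.842·√(0.30·0.70 + 0.15·0.85)]² / 0.15² = (1.157 + 0.489)² / 0.0225 = 120.5, so 121 per arm (242 per trial).
- Unpooled variance: n = 7.849 × 0.3375 / 0.0225 = 117.7, so 118 per arm (236 per trial).
- With continuity correction: 134 per arm (268 per trial).

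None gives 100.

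**2. Power of a comparison of proportions at 100 per arm**

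- Pooled: standard error under the null √(2·0.225·0.775/100) = 0.0591, under the alternative √(0.3375/100) = 0.0581. Then (0.15 − 1.960·0.0591)/0.0581 = 0.590, and Φ(0.590) = 72.2%.
- Unpooled: 0.15/0.0581 − 1.960 = 0.622, and Φ(0.622) = 73.3%.
- Exact enumeration: chi-square test 72.9%, Fisher's test 66.9%.

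**3. Are 30% vs 15% and HR 0.50 the same effect?** Under proportional hazards:

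- HR implied by 30% vs 15% = ln(0.85)/ln(0.70) = −0.1625/−0.3567 = 0.456.
- Intervention proportion implied by HR 0.50 = 1 − 0.70^0.5 = 16.3%.

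They are not the same.

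**4. Power of the planned log-rank test at 100 per arm**, with d events:

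- Schoenfeld: power = Φ(½√d·|ln HR| − 1.960)
- Freedman: power = Φ(√d·(1 − HR)/(1 + HR) − 1.960)

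| Effect | Expected events | Schoenfeld | Freedman | Simulated log-rank |
|---|---|---|---|---|
| 30% vs 15% (HR 0.456) | 30 + 15 = 45 | Φ(2.636 − 1.960) = 75.1% | Φ(2.509 − 1.960) = 70.8% | 73.1% |
| HR 0.50 (30% vs 16.3%) | 30 + 16.3 = 46.3 | Φ(2.359 − 1.960) = 65.5% | Φ(2.269 − 1.960) = 62.1% | 63.7% |

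The simulation used 20,000 runs with exponential times, censored at 6 months.

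**5. What 80% power would need with the log-rank test**

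- HR 0.50: Schoenfeld 4 × 7.849/(ln 0.5)² = 65.3, so 66 events; Freedman 7.849 × (1.5/0.5)² = 70.6, so 71 events. Dividing by the mean event proportion (0.30 + 0.163)/2 = 0.2317 gives about 285 or 307 patients per trial.
- HR 0.456: 51 events (Schoenfeld) or 57 (Freedman). Dividing by 0.225 gives about 227 or 254 patients per trial.

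**6. Effect detectable with 80% power at 100 per arm**, control 30%: HR 0.431 by Schoenfeld (14.2% re-admitted), 0.403 by Freedman (13.4%), about 0.42 by simulation. As proportions: 13.7%.

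**The case against.** The strongest reply accepts that 80% is not reached but disputes the size of the error. The hazard ratio of 0.50 is inferred from the halving of risk, so it can be read as a mislabelled risk ratio rather than a second design assumption. On that reading the design effect is 30% vs 15% and power is about 71–75%, a shortfall of 5–9 points. The effect that would give 80% is a fall to about 13–14% instead of 15%, a small difference for an effect that was partly presumed. This stands as a matter of emphasis: the 62–66% figure applies only if HR 0.50 is taken at face value. But the article prints HR 0.50 as the anticipated effect on the primary outcome and plans a log-rank test, so a reader is entitled to take it that way. The milder reading still does not give 80%.

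A second reply is that the sample-size section gives no time window for the 30%, and speaks of the number and duration of re-admissions, not time to the first. That is fair, and the event counts rest on the assumption stated above. It is the natural reading, given the 6-month period and the log-rank test on first re-admission.

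Other explanations fail. Loss to follow-up cannot account for the gap, because the register covers all patients and losses would only lower power. At HR 0.50, reaching 66 events with 200 patients would need a control proportion near 42%, against the 30% stated. A one-sided test would need about 95 per arm, close to 100, but the text says two-sided.

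**Conclusion.** The concern holds. No two-sided calculation from the printed inputs gives 80% power with 100 patients per arm. Power is about 71–75% for 30% vs 15% and 62–66% for HR 0.50, so the type II error is about 25–29% or 34–38% instead of 20%, in each trial. Fisher's test or a continuity correction would lower the first range further, to 66–67%. Separately, 30% vs 15% corresponds to HR 0.456, not 0.50, and that difference alone moves the power by about 9 points.

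The result assumes that 30% is the 6-month proportion with a first re-admission, that hazards are proportional and that follow-up is complete. The shortfall does not depend on which standard formula is used.

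**What to change.** Keep N = 200 per trial and restate the power paragraph:

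- Express the effect as one hazard ratio, to match the log-rank test, with the 6-month proportions that follow from it: HR 0.456 with 30% vs 15%, or HR 0.50 with 30% vs 16.3%. Drop the inference from a halved risk to HR 0.50.
- Give the expected number of first re-admissions, about 45 per trial, and say that the 30% refers to 6 months.
- State the power as about 71–75% for 30% vs 15%, or about 62–66% for HR 0.50. Alternatively, state the effect detectable with 80% power and name the formula: HR about 0.43 by Schoenfeld, 0.40 by Freedman.
- Revisit the sentence that gives cumulated duration a similar calculation, since it refers to the same figure.

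This costs wording only. It needs no extra patients and no change to conduct, but the trial must report lower power than it now claims. Keeping the 80% claim instead would take about 227–254 patients per trial for 30% vs 15% with the log-rank test, or about 285–307 for HR 0.50.

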### Randomization

#### Sequence generation

A computer-generated list of random allocation numbers using Pharma Consulting Group (http://www.pharmaconsultinggroup.com) will be generated. Patients included in the trial are randomized with a balanced allocation ratio of 1:1 to (1) using the Monsenso system, including the integrated feedback loop, based on a combination of subjective self-monitored measures and automatically generated behavioral data on measures of illness activity) including context-aware CBT modules (the intervention group) or to (2) standard treatment-as-usual (the control group) (Fig. 1).

Since the RADMIS trial is single-blinded, random block sizes are used to help preserve unpredictability [67, 68]. The RADMIS study nurses are unaware of the range of numbers in the block sizes.

The study will use a stratified design, where patients are stratified according to the psychiatric centres where patients are discharged from and according to the number of previous hospitalizations (three or less or more than three). The statistical analyses will adjusted for the two stratification variables, and also age and sex as possible prognostic variables. Further, in analyses on continuous variables, potential differences in baseline score on the outcome in question will be included as a potential confounder. If there are no statistically significant main effects of age and sex, these variables will be excluded from the final statistical analyses.

#### Allocation concealment and implementation

The allocation sequence is concealed from the researchers (e.g., [name]) enrolling and assessing the patients and from the RADMIS study nurses. Allocation is concealed in numbered, opaque and sealed envelopes.

### Blinding

Owing to the type of intervention in the RADMIS trials, the patient, the patients’ health care provider and the RADMIS study nurses are aware of the allocated randomization group. The researchers responsible for outcome assessments, data entry, data analyses, interpretation of analyses and writing of papers are kept blinded to allocation at all times during the trial period, data analyses and interpretation of analyses. The trials are, therefore, single-blinded. The RADMIS study nurses do not collect any outcome measures. At each visit with the researchers, all patients are thoroughly instructed not to mention anything about randomization allocation. In case of unblinding of the included patients’ allocation status, one of the other researchers blinded to intervention in the RADMIS trials will conduct the outcome assessments.

### Statistical methods

Data from all randomized patients are collected until dropout or the end of the trial period. Analysis will be carried out with an intention-to-treat (ITT) approach. The primary outcomes are differences in time to re-admission and duration of re-admissions during the 6-month trial period between the intervention group and the control group. Time to the first re-admission will be estimated using a Kaplan-Meier plot with reasons for censoring being date of death or end of study. The differences in cumulated prevention of re-admission in the intervention group and the control group will tested using a log-rank test. Analysis of secondary and tertiary outcomes will be done employing a linear mixed-effects model with random intercept for each participant and a fixed effect of visit. Differences in outcomes between the intervention group and the control group will be analyzed, firstly in an unadjusted model (except for differences in baseline values of the outcome variable in analyses on continuous variables) and then in models adjusted for the two stratification variables (1) psychiatric center and (2) the number of prior hospitalizations, and also for age and sex as possible prognostic variables. If there are no statistically significant main effects of age and sex, these variables will be excluded from the final analyses. Furthermore, subanalyses will be done employing a linear mixed-effects model with random intercept for each participant and a fixed effect of visit on differences in the HDRS-17 and the YMRS in patients with the presence of depressive and manic symptoms (defined as HDRS-17 > 0 or YMRS >0, respectively) at a given time point during the trial period between the intervention group and the control group. Additionally, in addition to analyses of the secondary outcomes, we will analyze differences in depressive and manic episodes defined as HDRS ≥14 and YMRS ≥14, respectively, during the trial period. Potential interactions between randomization group and visit number on any specific outcome variable in the analyses will be investigated and reported accordingly. The statistical threshold for significance is *p* ≤ 0.05 (two-tailed). Data will be managed by [name] and entered using Epidata®. All analyses will be done using SPSS, version 22.0 (IBM, New York, NY, USA) and STATA version 12 (StataCorp LP, College Station, TX, USA).

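### The only test named for time to first re-admission is a log-rank test without strata, despite stratified randomisation and promised adjustment; age and sex are kept or dropped on their p-values

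*Protocol article*

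**What the plan says.** All references are to the protocol article.

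- **Design.** The sections on trial design and on sequence generation stratify the 1:1 randomisation by discharging psychiatric centre and by prior hospitalisations (at most three versus more).
- **Promise to adjust (Sequence generation).** "The statistical analyses will adjusted for the two stratification variables, and also age and sex as possible prognostic variables". No outcome is exempted.
- **Primary analysis (Statistical methods).** "Time to the first re-admission will be estimated using a Kaplan-Meier plot with reasons for censoring being date of death or end of study". The test follows: "The differences in cumulated prevention of re-admission in the intervention group and the control group will tested using a log-rank test". Neither sentence mentions strata, covariates or a regression model.
- **Later in the same section.** After the linear mixed-effects model for secondary and tertiary outcomes, the text says that group differences in outcomes are analysed first without adjustment, with a second step described as "models adjusted for the two stratification variables (1) psychiatric center and (2) the number of prior hospitalizations, and also for age and sex".
- **Covariate rule (Statistical methods; same rule under Sequence generation).** "If there are no statistically significant main effects of age and sex, these variables will be excluded from the final analyses".

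**The concern.** Stratified randomisation makes the arms more alike on the stratification factors than simple randomisation would. A test that leaves the factors out still uses a variance that allows for chance imbalance on them. If they predict re-admission, that variance is too large, so the test rejects too rarely and loses power. Number of earlier hospitalisations is a plausible predictor of re-admission, which is presumably why it was chosen.

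The article also gives two instructions that are hard to carry out together: adjust for the strata, and test with a log-rank test for which no strata are named. If an adjusted re-admission analysis is intended, there are two results for the primary outcome and no statement of which one decides.

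The rule for age and sex is a separate weakness. Significance in one trial's data is a poor guide to whether a covariate is prognostic. The final model could differ between outcomes and between the unipolar and bipolar trials. In a Cox model, moreover, dropping a prognostic covariate changes the hazard ratio being estimated as well as its precision.

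**Working it through.** **1. The statements side by side.** Sequence generation: adjust for centre, prior hospitalisations, age and sex. Statistical methods, re-admission: Kaplan-Meier plot and log-rank test, nothing else named. Statistical methods, generic sentence: unadjusted, then adjusted; the only model named nearby is a linear mixed model, which does not handle a censored time. So no printed sentence says how the promised adjustment is done for re-admission.

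**2. Inputs.** From the section on statistical power and sample size: 100 per arm, two-sided alpha 0.05, risks 30% and 15%, hazard ratio (HR) 0.50. Under proportional hazards the two risks imply HR = ln(0.85)/ln(0.70) = 0.456. Expected events per trial: 100 × 0.30 + 100 × 0.15 = 45.

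Not in the document, so assumed: prognostic strength of the strata, six (or ten) equal centres, half the patients in each prior-hospitalisation group, and, where centre is a stratum, blocks of 4 and 6.

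**3. Test statistics.** At each event time, let p be the share of patients at risk who are in the intervention arm. The plain test is Z = Σ(g − p)/√Σp(1 − p), summed over events, with g = 1 if the event is in the intervention arm and 0 otherwise. The stratified test computes p within each stratum, then adds numerators and variances over strata. With six centres there are 6 × 2 = 12 strata, so on average 45/12 ≈ 3.8 events each; this sparseness is the possible cost of stratifying.

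**4. Simulated results, plain versus stratified** (control risk 30%, follow-up censored at 6 months).

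| Strata and assumed effects | Treatment HR | Power, plain / stratified | Change (points) | Type I error, plain / stratified |
|---|---|---|---|---|
| Prior hospitalisations only, stratum HR 2 | 0.456 | 72.3% / 73.3% | +1.0 | 4.8% / 5.1% |
| same, HR 3 | 0.456 | 70.8% / 72.7% | +1.9 | 4.8% / 5.9% |
| same, HR 5 | 0.456 | 69.5% / 73.6% | +4.1 | 3.5% / 5.3% |
| Both factors, 6 centres, no prognostic effect | 0.50 | 63.0% / 62.4% | −0.6 | 5.1% / 5.3% |
| same, HR 2, centre log-HR SD 0.3 | 0.50 | 62.3% / 63.9% | +1.6 | 4.7% / 5.3% |
| same, HR 3, SD 0.5 | 0.50 | 58.1% / 62.9% | +4.8 | 3.3% / 4.7% |
| same, HR 4, SD 0.5 | 0.50 | 56.9% / 64.6% | +7.7 | 2.9% / 4.6% |
| Both factors, 6 centres, no prognostic effect | 0.456 | 73.3% / 72.9% | −0.4 | – |
| Both factors, 10 centres, no prognostic effect | 0.456 | 73.2% / 71.8% | −1.4 | – |
| 6 centres, HR 2, centre not prognostic | 0.456 | 72.6% / 72.7% | +0.1 | – |
| 10 centres, HR 2, centre not prognostic | 0.456 | 72.1% / 72.2% | +0.1 | – |

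Rows with treatment HR 0.456 use 6,000 simulated trials, rows with 0.50 use 4,000. A further set with six centres, HR 0.456 and both factors gave changes of about −1 to +3 points. In that set strong prognostic effects took the plain test's type I error to about 3.4–4.0%, and stratifying restored about 5%.

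**5. Monte Carlo check.** At 5% and 6,000 trials the standard error is √(0.05 × 0.95/6000) = 0.28 points. The single stratified value of 5.9% is therefore (5.9 − 5.0)/0.28 ≈ 3.2 standard errors high. It did not recur: a repeat at stratum HR 3 gave 4.8%, and the other stratified values lie between 4.6% and 5.3%. I do not read it as real inflation.

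**6. What was not calculated.** The effect of the p-value rule for age and sex. That part rests on principle. All power values in the table are below the article's 80%; that is a separate sample-size question and carries no weight here.

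**The case against.** **The generic sentence may already cover re-admission.** It speaks of outcomes without limiting them to secondary and tertiary ones, and it confines the baseline exception to continuous variables, which suggests that other kinds of outcome are included. The log-rank test would then be the unadjusted first step. This reading is possible, so a reader who infers that the plan ignores the strata altogether goes beyond the text. It is not compelling either: the secondary outcomes include numbers of depressive and manic episodes, which are not continuous, so the exception makes sense without re-admission. On either reading the adjusted time-to-event model and the primary result are unstated.

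**No hazard ratio is planned.** A reader might infer this because the sample size rests on one and the analysis section reports none. A journal article commonly leaves the effect estimate and its interval to an analysis plan, which is not shown here. This is not a fault.

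**The covariate rule is prespecified.** It is mechanical, touches only age and sex, leaves both stratification factors in, and under Blinding the analysts do not know the allocation. This largely answers any suggestion that the rule lets the analysts pick a favourable treatment result. It does not answer the narrower point that the covariate set depends on the outcome data.

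**Stratifying is not free.** This stands: with no prognostic effect the losses were 0.4, 0.6 and 1.4 points.

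**Conclusion.** The point holds in a limited form. The article promises adjustment for the stratification factors, names only a log-rank test without strata for time to first re-admission, and does not say which result is primary if an adjusted one is added. It also fixes a p-value rule for age and sex that is poor practice.

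The plain log-rank test is valid. A reader might infer a false-positive risk; the calculations show the opposite, with type I error at or below about 5%. The loss is about 0 to 3 points of power under moderate assumed effects. Losses of about 4 to 8 points appear only under strong ones (prior-hospitalisation HR 5 alone, or HR 3 to 4 with marked centre differences). If the factors are not prognostic, stratifying costs about 1 point. These sizes depend on assumed prognostic strengths and centre numbers that the document does not give. The case for change rests on consistency and a single declared primary result, with a modest likely gain in power.

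**What to change.** In Statistical methods, for each of the two trials:

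- Make the primary test of time to first re-admission a log-rank test stratified by prior hospitalisations and centre. Pool small centres, or stratify by prior hospitalisations alone if centre strata are sparse. Settle this from patient numbers per centre, before the register linkage supplies the outcome.
- Take the adjusted effect from a Cox model with the same factors plus age and sex.
- Name the adjusted analysis as primary and the unadjusted one as sensitivity, and say explicitly whether the generic adjustment sentence covers re-admission.
- Delete the rule that excludes age and sex when not significant, here and under Sequence generation, and keep both whatever their p-values.

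The cost is wording. Both stratification variables are already needed for randomisation, and age and sex are already planned covariates. The downside is the pooling of sparse centres and up to about one point of power if the factors turn out not to be prognostic.
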